### Sample size calculation

We consider the demonstration of an intervention effect (for each of both interventions) on at least one of the primary endpoints for either the patient or the caregiver as a success. A pre-determined strict fixed sequence (FS) procedure defines the prospectively hierarchical ordering of the endpoints, for this study the hierarchical order is emotional functioning (1) and self-efficacy (2). Testing of null hypotheses proceeds according to their hierarchical order, that is, H(1)0 is tested first at a significance level of 5%, and if H*(*1*)*0 is rejected then H*(*2*)*0 is tested at the same significance level, otherwise H*(*2*)*0 is not tested at all. The strict FS approach has the highest power for testing the first hypothesis (outcome: emotional functioning) compared to the other methods, as it does not save any portion of alpha for testing later hypotheses [10]. The reference mean value for emotional functioning from EORTC for all cancer patients, stage III-IV is 71.5 (SD: 23.8) [28]. Alpha is set at 0.0125 instead of 0.05 to account for multiplicity (2 comparisons with control group * 2 participant groups [patients and caregivers]). We set 1-beta (i.e. statistical power) at 0.9. The expected difference between the control group and the intervention arms in the primary outcomes is 0.375 SD at T1 (12 weeks).

With these parameters *n* = 203 is needed in each arm across all countries (i.e. 609 in total). Anticipating a 65% retention rate at T1, which is more conservative than found in previous studies in the USA on the FOCUS interventions [5–7] due to the advanced cancer population included in this study, 938 dyads must be enrolled across the 6 countries (313 per group). This means that 156 dyads (i.e. 52 in each of the 3 arms) need to be enrolled in each country. Based on previous studies in the US [5–7] we expect an enrolment rate of 55% of those dyads referred to the study, meaning that about 282 dyads will need to be screened and identified in each country. The feasibility of recruitment has been evaluated based on previous research and discussions with clinicians in eligible hospitals.

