### Statistical methods/data analysis

#### Quantitative analysis

Four main analyses will take place.Primary hypotheses testing*Testing the null hypothesis of the first primary endpoint: emotional functioning.*

The effectiveness of the FOCUS+ face-to-face intervention and the iFOCUS web-based intervention will be compared with the standard care (control group) for each participant population (patients/caregivers) separately. In total, 4 comparisons are performed for one outcome variable (alpha = 0.0125). The hypotheses related to the first primary outcome (emotional functioning) will be tested using a mixed model (per participant population) with the T1 measurement value for emotional functioning as the outcome variable, recruitment center as random effect and randomization group, and the baseline measure of emotional functioning (T0) as predictor variables. We will perform analyses on both ‘intention-to-treat’ and per-protocol principles. The primary principle is intention-to-treat. After completion of the baseline measurement (T0), dyads will be randomized to one of the trial arms. All randomized dyads will be included in the mixed model. Multiple imputations will be applied. Predictors for the imputation model will include the baseline measurement, randomization group, age, and other variables (e.g. severity of the illness). The secondary principle is the per-protocol analysis that functions as a sensitivity analysis. The per-protocol population will be defined as dyads who have completed all sessions of the FOCUS+ or iFOCUS intervention (except for dyads in the control group) and T1 measurement. By including the baseline measurement as a predictor variable (ANCOVA), preexisting differences will be controlled for, enhancing the sensitivity of the analyses. To interpret the magnitude of the effects for the different outcomes, we will estimate effect sizes (Cohen’s d).b.*Testing the null hypothesis of the second primary endpoint: self-efficacy (the Lewis´ Cancer self-efficacy scale from FOCUS)*

As per the fixed sequence (FS) procedure, the null hypotheses of the second primary endpoint (self-efficacy) will only be tested if a significant result is found for the first primary endpoint (emotional functioning). The same strategy is then followed for the analyses as for the first primary endpoint, with an alpha level of 0.0125.(2)Secondary hypotheses testing

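### The gate from emotional functioning to self-efficacy is not tied to the matching comparison; read literally, it does not hold the eight-test primary family at 5% when one to three emotional-functioning effects are real

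*Protocol article*

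**What the plan says.** The section on sample size calculation sets up a strict fixed sequence: "for this study the hierarchical order is emotional functioning (1) and self-efficacy (2"). It is written for a single pair of hypotheses. "H(1)0 is tested first at a significance level of 5"%, and the second hypothesis follows at the same level only if the first is rejected; otherwise it is not tested. The same paragraph then says "Alpha is set at 0.0125 instead of 0.05 to account for multiplicity", the multiplicity being two comparisons with control in each of two participant groups. It also counts a demonstrated effect "on at least one of the primary endpoints for either the patient or the caregiver as a success", with a parenthesis saying that this applies for each of the two interventions.

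The section on quantitative analysis confirms the count for EF: "In total, 4 comparisons are performed for one outcome variable (alpha = 0.0125"). On SE it says that "the null hypotheses of the second primary endpoint (self-efficacy) will only be tested if a significant result is found for the first primary endpoint", and then: "The same strategy is then followed for the analyses as for the first primary endpoint, with an alpha level of 0.0125".

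So each endpoint has four null hypotheses, eight in all. The gate refers to the SE hypotheses in the plural and to a single significant EF result. No section says whether that result must be any one of the four, all four, or the one for the same intervention and population.

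**The concern.** A fixed sequence keeps its error rate because a later hypothesis is reached only through rejection of the one before it in the same sequence. Dividing 5% by four gives four sequences of 0.0125 each. That protects the whole family if each SE test waits for its own EF test. If one EF rejection opens all four SE tests, three of them are reached without a rejection in their own sequence and receive alpha that nothing has released.

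At stake is which confirmatory SE claims the trial may make. On the literal wording, SE could be declared for web-based iFOCUS in caregivers because nurse-led FOCUS+ improved EF in patients. If the gate stays open to interpretation, the choice of reading could be made after the results are known.

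The success statement has a related fault. It treats SE as an alternative way to succeed, while the strict sequence lets SE be tested only after EF has succeeded.

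**Working it through.** **Inputs from the protocol.** Alpha 0.0125 per comparison, two-sided; power 0.90; effect 0.375 SD on the primary outcomes at T1; 1:1:1 allocation; n = 203 per arm.

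**Reproducing the plan's figure.** n per arm = 2 × [(z for 1 − 0.0125/2 + z for 0.90) / 0.375]² = 203.13, against the stated 203. At n = 203 the power is 0.8998. With alpha 0.05 the formula gives 150 per arm, so 0.0125 is the level actually used.

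**Error bound on the literal gate.** Let k be the number of EF comparisons with a real effect, detected with power near 1, and let all SE nulls be true. Testable true nulls = (4 − k) EF tests, plus 4 SE tests once k is at least 1. Bound = 0.0125 × that number; under independence, error = 1 − 0.9875 to that power.

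| Real EF effects | Testable true nulls | Bound | Independent |
|---|---|---|---|
| 0 | 4 | 5.0% | 4.9% |
| 1 | 3 + 4 = 7 | 8.75% | 8.43% |
| 2 | 2 + 4 = 6 | 7.5% | 7.27% |
| 3 | 1 + 4 = 5 | 6.25% | 6.10% |
| 4 | 0 + 4 = 4 | 5.0% | 4.9% |

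With k = 0, an SE error can occur only after a false EF rejection that is already counted, so the four EF tests set the limit.

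**One real EF effect at the planned 90% power, independent tests.** 1 − 0.9875³ × (0.9 × 0.9875⁴ + 0.1) = 7.96%.

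**With correlation.** The eight z-statistics were simulated with 1,000,000 draws per setting. The correlation between arms is 0.5, from the shared control and equal allocation. The patient–caregiver and EF–SE correlations are not in the protocol; values of 0, 0.3 and 0.5 were assumed for each.

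| Scenario (all SE nulls true) | Literal gate | Matched gate |
|---|---|---|
| No real effect | 4.4–4.7% | 4.4–4.7% |
| One real EF effect of 0.375 SD | 6.8–7.7% | 4.3–4.7% |
| One real EF effect, power near 1 | 7.4–8.1% | 4.6–4.8% |

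In about 3% of trials with one real EF effect of 0.375 SD, the literal gate produced a false SE claim for a comparison whose own EF test had failed.

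**Why the matched gate holds 5%.** In each chain, if the EF null is true, a false claim requires a false EF rejection, with probability at most 0.0125. If the EF effect is real, the only possible false claim is SE, again at most 0.0125. Over four chains: 4 × 0.0125 = 5.0%, whatever the pattern of real effects.

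**SE power.** With matched gates and both effects at 0.375 SD, independence of EF and SE gives 0.90 × 0.90 = 0.81; simulation over the assumed correlations gives 0.81–0.83. Under the literal gate it is about 0.90, because some EF test almost always succeeds when all effects are real.

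**Success rule.** Under the matched gate, rejecting SE implies that EF was rejected in the same comparison, so success on at least one primary endpoint reduces to success on EF. Under the literal gate, an intervention could succeed on SE alone because the other intervention opened the gate.

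**The case against.** The strongest reply is that the fixed sequence is defined for one pair of hypotheses and that the quantitative analysis section invokes that procedure by name. Applied comparison by comparison, this gives four EF-then-SE chains at 0.0125, which hold 5%. That reading is open, so the documents do not support a flat statement that the plan fails to control its error. What stands is that the protocol does not fix that reading, and that its gate sentence, taken as written, describes a rule that does not control the error. The gate is stated here, so this is not merely a detail left to an analysis plan that is not shown.

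Second, the inflation depends on the pattern of effects. The protocol plans 0.375 SD for both interventions and gives both the same core content, aimed at dyads. If all four EF effects are real, error stays below 5%. A reader might infer that an effect confined to one arm and one population is the likely outcome; nothing in the protocol supports that. It is a possible pattern that the procedure should cover.

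Third, a reader might infer that the plan both inflates error and loses SE power. Each harm belongs to a different reading: inflated error with SE power near 0.90 on the literal gate, or controlled error with SE power of 0.81–0.83 on the matched gate.

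Fourth, a reader might take the 5% in the sequence as the level of each comparison. The same paragraph replaces 0.05 with 0.0125, the analysis section uses 0.0125 for both endpoints, and only 0.0125 reproduces 203. The 5% can be read as the level for an endpoint's four tests together, so this is wording to reconcile and not a second error.

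**Conclusion.** The point holds in a limited form. The gate is not tied to the matching comparison. On its literal reading the eight-test primary family is not held at 5% when one to three EF effects are real and the SE nulls are true. The excess is largest with one real EF effect: a bound of 8.75%, and about 6.8–7.7% at the planned 0.375 SD. The simulated range rests on n = 203 per arm and on assumed patient–caregiver and EF–SE correlations of 0 to 0.5; the bound needs no correlation assumption.

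The mismatch between the success rule and the strict sequence is real. Under matched gates it permits no extra claim, but it describes a route that does not exist. The primary EF analysis and its sample size are unaffected.

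**What to change.** - Define four chains: FOCUS+ in patients, FOCUS+ in caregivers, iFOCUS in patients, iFOCUS in caregivers. In each, test EF at 0.0125, and test SE at 0.0125 only if EF in the same chain is significant.
- State 5% as the family level and 0.0125 as the per-comparison level, and remove the 5% from the description of a single test.
- Restate success, separately for each intervention, as a significant EF effect in patients or in caregivers, with SE confirmatory after that.
- State the 90% power for EF only, and report the lower chance of claiming a given SE effect calculated above.

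Reallocating alpha from a chain in which both hypotheses are rejected to the remaining chains is an optional refinement; error control does not depend on it.

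The cost is a change of wording in the protocol and analysis plan, made before unblinding. No extra dyads are needed. The success statement becomes narrower, and SE can no longer be claimed for a comparison that failed on EF.

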All identified secondary endpoints (Quality of Life [including separate items of hopelessness, anxiety, depression], benefits of illness, coping, dyad communication, all at T1) will be evaluated by testing the FOCUS+ and iFOCUS against care as usual (control group) for each participant population (patients/caregivers) separately. In total, 4 comparisons are performed for each outcome variable. For each secondary outcome variable, a mixed model is applied with the T1 measurement value as the outcome variable, recruitment center as random effect, and randomization group and baseline measurement of the variable (T0) as predictor variables. We will perform analyses on both ‘intention-to-treat’ and per-protocol principles, applying the same principles as described above.

By including the baseline measurement as a predictor variable (ANCOVA), preexisting differences will be controlled, enhancing the sensitivity of the analyses. To interpret the magnitude of the effects for the different outcomes, we will estimate effect sizes (Cohen’s d). All statistical tests will be two-sided and considered significant if *p* < 0.0125.

All primary outcomes and secondary outcomes as listed above will also be analysed at T2 (6 months) to evaluate longer-term effects, using the same analysis procedures.

The cost-effectiveness of the interventions will be determined by analyzing patterns and costs of healthcare utilization and effects on quality of life. Costs will be estimated by combining the reported frequency of health care use by participants with country-specific unit costs for each service domain. Quality of life will be measured by combining EQ5D5L with country-specific preference weights. We will evaluate the robustness and consistency of results in population-specific outcome measures EORTC, FACT-G and CQOLC. Data will also be collected on the types and amounts of informal care provided to patients in each arm of the study, to investigate if the amount or patterns of informal care change as a result of the intervention. The outputs will be mean costs of care for patients in each arm of the study, cost per year of life gained (if survival is affected significantly by the intervention and the costs in the intervention groups overall are higher), and (if appropriate) the additional costs of achieving a better quality of life outcomes (including estimates of cost per quality-adjusted life-year gained).(3)Exploratory hypotheses testing

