For all exploratory endpoints, two-sided statistical tests will be considered significant if *p* < 0.05.

For the outcomes that are measured identically for the patient and the caregiver, we will assess the effect on the dyad as a whole (i.e. both patient and family caregiver). For the outcome instruments that led to comparable estimated differences between FOCUS+ and standard care and iFOCUS and standard care, the effect will be assessed on the dyad as a whole by adding an extra level (dyad) to the linear regression model.For each of the primary and secondary endpoints, subgroup analyses will be performed using formal interaction tests to explore the extent to which the outcomes of the trial differ by country, gender, and socioeconomic status. Interaction terms between respectively country, gender, and socioeconomic status on the one hand and the trial arms on the other hand will be added to the analysis models. For the country variation multilevel mixed model analyses will also be performed to additionally account for potential clustering by country (i.e. participants nested within a country). Outcomes will be analysed with country as random factor.(4)Other analysesBackground reports describing care as usual for people with advanced cancer will facilitate the understanding of the results of the between-country comparisons.Process evaluation of the implementation of the interventions will be analyzed following the MRC framework for evaluating complex interventions [30], integrating normalization process theory (NPT) [31] and the RE-AIM framework [32]. Data analysis for the process evaluation will include a) standard statistical descriptions of the quantitative data from the intervention checklist and routine monitoring to describe adherence to the implementation. This analysis will determine cut-off points for good intervention adherence and, hence, inform the per-protocol analyses; b) analyses of the qualitative data (semi-structured interviews with patients and their family caregiver and post-intervention interviews with the nurses who delivered the face-to-face FOCUS+ intervention) will be performed (see below - Qualitative analysis).

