## Discussion

This project aims to study the effect of two psycho-educational interventions on emotional functioning and self-efficacy of patients with advanced cancer and their informal caregivers. DIAdIC is a large-scale study conducted across different countries and provides knowledge about intervention dosage and different modes of administration. Psychosocial support and education for people with advanced cancer and their family caregivers can substantially reduce their distress, improve their QoL, and prevent avoidable health resource use [4, 8]. Often, family caregivers have a double role: as a provider of care to the person with cancer, but also as a person in need of support for themselves [33]. Both interventions focus on the empowerment of non-professionals (the family caregiver and the patient with advanced cancer) by improving their mutual communication, assisting them to identify positive aspects related to their situation, and increasing their self-efficacy.

Few studies have systematically assessed the cost-effectiveness of large scale psychosocial and psychoeducational interventions. As the cost-effectiveness of the interventions will be determined by analyzing patterns and costs of healthcare utilization and effects on QoL, the results of this RCT can thus contribute to the search for cost-effective novel interventions that can relieve constraints on professional healthcare.

The cross-country setup in six European countries allows for a comparison of the effectiveness of the interventions in different healthcare systems and regimes across Europe. The DIAdIC interventions are complex interventions where contextual factors such as country-specific healthcare systems and dyad characteristics influence the mechanisms of action of the interventions. Therefore, a thorough process evaluation following the normalization process theory and the RE-AIM framework is embedded in the study. This analysis will determine cut-off points for good intervention adherence and, hence, inform the per-protocol analyses.

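### The exploratory dyad analysis is limited to outcomes whose observed FOCUS+ and iFOCUS effects look comparable: a results-dependent condition that, read literally, compares interventions when it should compare patients with caregivers

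*Protocol article*

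**What the plan says.** The passage is part (3), exploratory hypotheses testing, under Quantitative analysis in the protocol article. Two adjacent sentences matter.

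- The first has no condition: "For the outcomes that are measured identically for the patient and the caregiver, we will assess the effect on the dyad as a whole".
- The second specifies the model, a linear regression with dyad as an added level, but only for a subset of instruments. Its restriction reads: "For the outcome instruments that led to comparable estimated differences between FOCUS+ and standard care and iFOCUS and standard care".

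The differences in the second sentence are results of the main analyses earlier in the same section, where each intervention "will be compared with the standard care (control group) for each participant population (patients/caregivers) separately". The text gives no margin, test or assessor for the word comparable, and does not mention comparability between patients and caregivers. The analysis belongs to the exploratory tier, tested two-sided at the 0.05 level.

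Table 4 lists emotional functioning, self-efficacy, benefits of illness, coping and dyad communication with the same item counts in both roles. The quality-of-life instruments differ by role.

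**The concern.** There are two problems.

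**Selection on results.** Under the second sentence, an outcome receives a dyad estimate only after its arm effects have been seen. This sits badly with the unconditional sentence just before it. The dyad is the randomized unit and the target of both interventions, so readers will look for dyad results. They could find them only for outcomes picked by an unstated judgement on the observed data.

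**The condition does not protect the pooled estimate.** Adding a dyad level and pooling the two roles gives one effect per arm, averaged over patient and caregiver. That average describes both people only if the arm acts similarly on both. Similarity of FOCUS+ and iFOCUS is not needed, because each arm is compared with control. A rule based on similarity of the arms can admit outcomes where the roles diverge and block outcomes where pooling would be harmless.

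**Working it through.** **Inputs from the protocol article (Sample size calculation).** Two-sided alpha 0.0125, power 0.9, effect 0.375 SD, 203 analysed per arm, 65% retention at T1.

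**Reproducing the plan's figure.** n per arm = 2(z₀.₉₉₃₇₅ + z₀.₉)² / 0.375² = 2(2.498 + 1.282)² / 0.1406 = 203.1. The stated 203 reproduces (204 if rounded up), and 203 / 0.65 = 312.3, so 313 enrolled per arm, as stated. These figures are not in dispute; 203 is used only as the n below.

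**Assumptions not in the document.** SD 1, unadjusted mean differences, patient-caregiver correlation 0.3, and comparable taken as a FOCUS+ versus iFOCUS gap below 0.1 SD or 0.2 SD in both roles.

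**Step 1: what the rule measures.** Within one role, (FOCUS+ − control) − (iFOCUS − control) = FOCUS+ − iFOCUS, because the control mean cancels. Its standard error is √(2/203) = 0.0993 SD.

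**Step 2: equal true effects in the two arms.** In one role the pass probability is 2Φ(c/0.0993) − 1:

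- c = 0.1: 2Φ(1.007) − 1 = 0.686
- c = 0.2: 2Φ(2.015) − 1 = 0.956

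Passing in both roles (bivariate normal, correlation 0.3) has probability 0.482 and 0.916. Chance and the unstated cut-off therefore largely decide which outcomes are analysed.

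**Step 3: both arms help patients by 0.375 SD and caregivers by 0.** The arms are equal within each role, so Step 2 applies and the outcome passes 48% to 92% of the time. The pooled effect is (0.375 + 0)/2 = 0.1875, about 0.19 SD, which describes neither role.

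**Step 4: FOCUS+ gives 0.375 SD in both roles, iFOCUS gives 0.** Pooling the roles is harmless here. The gap is centred on 0.375 SD. In one role the pass probability is about Φ((c − 0.375)/0.0993):

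- c = 0.1: Φ(−2.77) = 0.003
- c = 0.2: Φ(−1.76) = 0.039

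Passing in both roles has probability 0.0001 and 0.005, so under 1%.

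**Step 5: the same two cases if patients are compared with caregivers within each arm** (simulated, correlation 0.3):

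| True effects | Arm-versus-arm rule | Patient-versus-caregiver rule |
|---|---|---|
| 0.375 SD in patients, 0 in caregivers, both arms | 48% to 92% | 0.1% to 1.9% |
| FOCUS+ 0.375 SD in both roles, iFOCUS 0 | under 1% | 40% to 84% |

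The literal rule sorts these two cases the wrong way round.

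**Step 6: false positives.** With no true effects, the pooled standard error is √(1.3/203) = 0.080 SD. Among outcomes that pass the arm-versus-arm rule, the dyad test of one arm rejects at 5% in 3.0% (c = 0.1) or 4.2% (c = 0.2) of simulated trials. The rule does not inflate type I error.

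**Sensitivity.** For correlations from 0.2 to 0.5 the Step 3 pass rates are 48% to 50% (c = 0.1) and 92% (c = 0.2), and the Step 4 rates stay under 1%. Baseline adjustment would shrink the standard error. That would raise the Step 3 rates and lower the Step 4 rates, so the pattern would hold.

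**The case against.** **The sentence is loose.** It follows one about outcomes measured identically in patient and caregiver, and the contrasts come from separate patient and caregiver models. The authors may have meant that each contrast should be comparable across the two roles, which is the condition pooling needs. This stands: the charge of a wrong comparison holds only on the literal reading. On the other reading the wording needs correcting, and selection on results remains.

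**The first sentence is unconditional.** It is therefore not settled that dyad results will exist only for a subset. This also stands, and it is why the two sentences must be reconciled.

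**The stakes are limited.** The analysis is exploratory. Role-specific effects are planned for every outcome in any case, with self-efficacy subject to the fixed sequence. Success is defined on either the patient or the caregiver. All of this is correct and bounds the point.

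**A missing threshold is detail for an analysis plan.** That is fair for the margin alone. The article does more than omit a margin, however: it states a results-dependent rule.

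**A reader might infer that the rule produces extra false positives.** If one keeps outcomes whose two arm z-statistics lie within 0.5 of each other (an illustrative cut-off, null effects, correlation 0.5 from the shared control), the chance that both arms are significant does rise from 0.9% to 1.7%. This shows only that selecting on similarity makes the arms agree more often. In the same setting the per-test rate falls from 5.0% to 2.5%.

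**A reader might also infer that a mode-of-delivery conclusion will rest on this judgement,** because the Discussion says the study "provides knowledge about intervention dosage and different modes of administration". The documents do not support that. The Objectives and Trial design sections plan comparisons with usual care only, and nothing links the word comparable to a claim about FOCUS+ against iFOCUS.

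**Conclusion.** The point holds in a limited form. Two adjacent sentences disagree on which outcomes get a dyad analysis, and the second makes the answer depend on observed effects. Read literally, it also applies a criterion that does not bear on whether patient and caregiver effects can be pooled.

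The harm is selective and potentially misleading dyad estimates. At 203 per arm, an outcome helping patients only would be pooled 48% to 92% of the time, at about 0.19 SD. An outcome where only FOCUS+ works, equally in both roles, would almost never be analysed at dyad level. The percentages rest on the assumed correlation and cut-offs; the direction does not.

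Nothing here touches the primary or secondary tests, their alpha of 0.0125, or the sample size. The point deserves correction because the dyad is central to the trial and the correction is cheap.

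**What to change.** Delete the condition about comparable differences. For every outcome measured identically in patient and caregiver, fit one joint model with a dyad level, role, arm, role-by-arm interaction, baseline value and recruitment centre. Whatever the results, report for each arm versus control:

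- the dyad-average effect,
- the role-by-arm interaction,
- the patient and caregiver effects separately.

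The interaction and the role-specific effects then show directly whether the average is a fair summary, so no gate is needed. Keep the analysis labelled exploratory.

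The cost is a change of wording and one extra exploratory model per outcome on data already collected, with no change to design, sample size or confirmatory testing. A FOCUS+ minus iFOCUS contrast could be read from the same model, but it would be an additional estimand and is not part of this correction.
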